## 3.0 OBJECTIVES

## 3.1 Primary Objective

The primary objective of the study is to assess if there is a mucosal response to 14 daily applications of 1% tenofovir gel or matched placebo gel in low-risk, sexually abstinent, HIV-negative women by examining cervicovaginal secretions for changes in cytokines, chemokines, and other mediators of innate immunity.

**3.2 Secondary Objectives**

A secondary objective is to determine whether the intrinsic antimicrobial activity of CVL to HSV, *E. coli* and *Staphylococcal aureus* is altered following 14 days of daily intravaginal application of 1% tenofovir or matched placebo gel compared to antimicrobial activity at baseline. If changes are observed, we will explore whether changes in the concentration of specific mediators correlate with the observed change in antimicrobial activity.

An exploratory objective is to measure the concentration of tenofovir in serum, CVL and cells following repeated daily intravaginal application of 1% tenofovir gel.

**4.0** **STUDY DESIGN**

This is a single-center, double blind randomized study of 1% tenofovir gel and matched placebo gel to be conducted among 24 women. The female participants will have a normal gynecological history, regular menstrual cycle with at least 21-day cycles, and be at low risk for HIV or other STI. Participants will be randomized to apply 1% tenofovir gel or matched placebo gel once daily for 14 consecutive days between menses. Gilead Sciences, Inc. (Foster City, CA) will provide 1% tenofovir and matched placebo gels. The randomization will be 1:1 (i.e., 12 in each treatment arm). The Albert Einstein College of Medicine Research Pharmacy will provide the randomization procedure. Participation in this study will last approximately two months.

Prior to screening, potential participants will be informed of the need to abstain from insertion of anything into their vagina from 48 hours prior to the enrollment visit until completion of the study. Women unwilling or unable to assure abstinence will not be enrolled. Participants must agree to abstain from vaginal or anal intercourse or insertion of sexual toys. They must also agree not to douche or use any vaginal product other than the investigational product (including lubricants, feminine hygiene products, and vaginal drying agents) for 48 hours before enrollment and for the duration of the study (21 days).

At the screening visit, eligible volunteers will come to the General Clinical Research Center (GCRC) at the Montefiore Medical Center (MMC)/Albert Einstein College of Medicine (AECOM). After informed consent is obtained, a medical, gynecological, and sexual history will be obtained. Urine will be collected for microscopy, culture, and a pregnancy test. If the pregnancy test is negative, a pelvic examination will be performed including a speculum exam with visual inspection, pH measurement, wet prep, and collection of a baseline cervicovaginal lavage (CVL) sample. CVL is a wash of the cervicovaginal area using 10 ml of phosphate buffered saline (PBS). A 10 ml syringe filled with PBS is aimed directly at the cervical os and posterior vaginal wall. The pooled fluid is aspirated and the entire volume collected. A Pap smear will be obtained if documentation of a negative result within the last year is not available. A cervical swab (DNA probe) for *N. gonorrhoeae* and *C. trachomatis* will be done. A bimanual exam will be performed for adnexal masses or tenderness. If there is evidence of a clinically detectable genital abnormality (i.e., ulcer, lesion or positive wet mount) or urinary tract infection, appropriate treatment and follow-up will be provided and the volunteer will be ineligible to continue in the study at this time. If a lesion or ulcer is present at this or any visit, a herpes culture will also be sent. Blood will be collected for a pregnancy test, HIV EIA, RPR, HSV serologies (type common and type-specific; Focus Technologies, Herpes Select), hepatitis B surface antigen, hepatitis B core immunoglobulin M (IgM) and hepatitis B core immunoglobulin G (IgG) (See Appendix I). Blood will also be collected for progesterone and estradiol levels to determine the phase of menstrual cycle (proliferative phase defined by serum progesterone  3 ng/ml) and to assess kidney and liver function. Subjects with no contraindications to study participation will be presumed eligible for enrollment.

On the day of Enrollment (Day 0) (2-6 days after the next menses, within 30 days of screening), participants will return to the GCRC. Test results from screening will be reviewed. Urine will be collected for a repeat pregnancy test. If the pregnancy test remains negative, a speculum exam will be performed and the vagina and cervix will be visually inspected. A pH sample from the vaginal wall and a gentle swab for wet prep will be obtained. If there is evidence of a clinically detectable genital abnormality (i.e., ulcer, lesion or positive wet mount) appropriate treatment and follow-up will be provided and the participant will be ineligible to participate further at this time. If there is evidence of recent intercourse (sperm visualized on wet mount slide or positive PSA-specific membrane test), the participant will be ineligible to continue in the study. If there is evidence of acute or chronic hepatitis B infection or liver or kidney abnormalities, the participant will be ineligible to continue in the study. If the patient is eligible, a baseline CVL will be collected. Participants will be randomized in a double blind manner to receive the 1% tenofovir gel or matched placebo gel. The participant will insert one dose of study gel intravaginally under the guidance of the study clinician. Provided that the first dose is well tolerated, subsequent applications will be inserted once daily (preferably at bedtime) by the participants (see Appendix III) for 13 consecutive days. Subjects will be instructed and frequently reminded to apply each daily dose at bedtime. Study gels will be provided in single-use tubes with separate vaginal applicators and the participant will be provided with a study diary to record usage, symptoms and reasons for non-adherence.

Every effort will be made to bring participants back after 3, 7 and 14 doses of drug or placebo. Visits will be scheduled in the GCRC on Day 3 (range, days 2-4), Day 7 (range, days 5-9) and Day 14 (range, days 12-15). If a subject misses a dose, she may return on Day 15. There will be a Final Visit scheduled on Day 21 (range, days 16-21), prior to the anticipated onset of menstruation. A pelvic exam will be performed at each visit. CVL samples will be obtained at the Screening Visit, on Days 0, 3, 7, 14, and at the Final Visit (Day 21). Symptoms of vulvar or vaginal soreness or pruritus, vaginal bleeding, dysuria, or acts of vaginal penetration will be documented by participants in a study diary, which will be provided. Participants will be asked to record information on the number of times they administer study gel, time of each insertion, emergence/resolution of specific symptoms and reasons for non-adherence. Diaries will be reviewed at each visit. Participants will bring used and unused supplies with them to each visit for counting and disposal. Adverse events will be recorded as described in Section 8.0. Subjects will receive $25 for the Screening Visit and $50 for all other scheduled study visits (Enrollment Visit, Day 3 Visit, Day 7 Visit, Day 14 Visit and Day 21 Visit) (total $275) as compensation for their time and travel expenses.

**4.1 Laboratory Methods**

Cervicovaginal lavage specimens will be immediately transported on ice to the investigators’ laboratories and centrifuged for 20 minutes at 1000 g at 4C. Antibiotics and protease inhibitors will be added and the supernatant will be aliquoted and stored at -80C. Cell pellets will be resuspended in 1 ml of PBS. Leukocytes from CVL samples will be stained using a panel of differentially conjugated monoclonal antibodies (mAbs) against various human leukocyte membrane antigens and analyzed by seven-color fluorescent activated cell sorter (FACS). The mAbs used will include Abs directed against CD45 (hematopoietic cells), CD19 (B cells), CD3, CD4, CD8 (T cells), CD14 (macrophages), and CD11 (dendritic cells) (Becton Dickinson, Franklin Lakes, NJ). Cell preparations will be labeled in parallel with appropriate isotype control Abs (Becton-Dickinson). If insufficient cells are obtained for FACS, an alternative strategy is to use immunohistochemistry; a portion of the cell suspension is smeared onto 8-well teflon-coated slides, fixed in absolute methanol and stored at -70°C for immunohistological studies of cell populations. Cytokines and chemokines in CVL supernatants will be quantified using a multiplex Luminex assay (Biosource), which allows for the quantitative measurement of multiple cytokines or chemokines using a small sample size. The following mediators will be measured by Bioluminex: IL-1, IL-1, IL-2, IL-6, IL-8, IL-10, IL-12, interferon-alphabeta (IFN-), IFN-, TNF-, macrophage inflammatory protein-1alpha (MIP-1), MIP-1, regulated upon activation, normal T cell expressed and secreted (RANTES). IgG, immunoglobulin A (IgA), SLPI, TGF-, IL-1ra, lactoferrin and HNP1-3 will be measured using commercial ELISA kits (R & D Systems, Minneapolis, MN) and HNP-4, HD-5, HD-6 and the hBDs using ELISA or semi-quantitative Western blotting developed in [name] laboratory. These mediators were selected because of their potential to influence mucosal immunity and ability to be detected in CVL based on our prior studies.

CVL will also be assayed for intrinsic anti-HSV activity. Human cervical epithelial cells (CaSki) will be treated with each CVL sample (diluted 1:2 in serum-free media) for 1 h and then challenged with serial dilutions of HSV-2(G) in triplicate. The viral titer (pfu/well) in the presence of each CVL sample or control buffer will be determined by counting plaques 48 h pi. The effects of CVL pre- and post-application of tenofovir or placebo gel on the growth of *Escherichia coli* ML-35 and *Staphylococcus aureus* will also be examined. Stationary phase bacterial cells will be washed 3 times with PBS (pH 7.4) and 10 µl of 2 X 109 CFU/ml (2 X 107 CFU) will be incubated with an equivalent volume of CVL or control fluid (1.5 mg/ml BSA in saline containing the same concentrations of penicillin and streptomycin as CVL) at 37C for 2 h. Aliquots of bacteria will be removed, subjected to sequential serial dilutions with PBS and further diluted into 5 ml of a 43C solution of 1% agarose in PBS and 1% trypticase soy broth. After rapid dispersion of bacteria, the bacteria-containing 5 ml agar sample will be poured over a trypticase soy agar underlay. Colonies will be counted using ImageQuant TL v2005 after an overnight incubation at 37C and relative number of colonies will be compared.

Given that systemic tenofovir absorption occurred in the Phase I HPTN 050 trial, tenofovir levels will be measured in serum, CVL supernatants and CVL cell pellets following repeated application of 1% tenofovir gel or matched placebo. Blood samples will be collected in potassium EDTA tubes and plasma will be separated by low speed centrifugation for 15 minutes at 4C. Plasma will be carefully transferred to sterile cryovials and stored at -70C until analysis. Plasma and CVL tenofovir levels will be quantified using an optimized solid-phase extraction procedure combined with a rapid reverse-phase high-performance liquid chromatography method and photodiode array detection. This accurate and sensitive method has been validated in human blood plasma [28]. The high extraction efficiency (98.6%), low limit of quantification, and wide linear dynamic range (10-10,000 ng/ml) make this a suitable method for use in a clinical trial. This method has been used previously on cervicovaginal fluid, which was collected via direct aspiration with a vaginal aspirator. It has not been validated in CVL to the same extent as the plasma assay.

**5.0 STUDY POPULATION**

Twenty-four healthy women will be enrolled in this study. Participants will be selected for this study and recruited according to the criteria below. Conditions for withdrawal from the study are described in Section 13.

Subjects will be recruited from the catchment area of the MMC, which is centered around 2 hospital campuses, the Montefiore Hospital and the Weiler Hospital. There is a diverse ethnic distribution consisting of 48% Hispanics, 36% Blacks and 7% Whites. The diversity of the population in our catchment areas permits the recruitment of patients from most of the major ethnic groups including Asians and Pacific Islanders, Blacks, Hispanics from Mexico, Puerto Rico, Cuba and Central and South America and Caucasians.

The study will be conducted at the General Clinical Research Center (GCRC) at the MMC/AECOM. Participants will be referred by providers from the Internal Medicine, Adolescent and Gynecology Clinics at MMC. IRB-approved advertisements will be posted to recruit self-referrals. Potential subjects will contact the study staff to discuss the details of the study, including inclusion criteria, and to schedule screening appointments.

# 5.1 Participant Inclusion Criteria

# Women who meet all of the following criteria (by self-report, unless otherwise specified) are eligible for inclusion in this study:

- Age  18 and 50.
- Able and willing to provide written informed consent to participate in the study (Given the demographics of our study population, a Spanish consent form and diary will be prepared).
- Normal menstrual history with regular cycles with a minimum of 21 days between menses.
- Low risk for HIV/STI infection. Low risk is defined as

1. Not having had an STI in the last 6 months.
2. Not having used non-therapeutic intravenous drugs in the last year.
3. Being either sexually abstinent or being in a stable, mutually monogamous relationship with a partner who is not known to be HIV positive.

- Agree to the insertion of 1% tenofovir gel or matched placebo gel.
- Agree to abstain from sexual intercourse and to not use vaginal products for 48 hours prior to enrollment and for the duration of the study (through the Final Visit).

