# 5.2 Exclusion Criteria

Women who meet any of the following criteria (by self-report, unless otherwise specified, at screening, enrollment, or at anytime during participation, unless otherwise specified) will be excluded from this study:

- Are pregnant (based on a urine pregnancy test) or less than 6 months post-partum.
- Are currently breastfeeding.
- Are menopausal.
- Are currently using hormonal contraception or have used hormonal contraception in the previous 2 months.
- Are currently menstruating (at screening or enrollment visits – may be eligible for deferment).
- Have a positive HIV test at screening.
- Have a positive urine culture at screening (may be eligible for re-screening after treatment).
- Have a positive chlamydia, gonorrhea, or trichomonas result at screening.
- Have an abnormal Pap smear (if documentation of a negative result within the past year is not available).
- Have a clinically detectable genital abnormality (i.e., vulvar, vaginal, cervical and/or perianal ulcer and/or lesion or an abnormal wet mount).
- Have a history of Toxic Shock Syndrome, or a history of symptoms suggestive of Toxic Shock Syndrome.
- Have a history of intermenstrual bleeding in the 3 months prior to enrollment.
- Have had gynecological surgery or received treatment for syphilis, genital herpes, chlamydia, gonorrhea, trichomonas, or genital warts in the last 6 months.
- Have received treatment for candida, bacterial vaginosis, or urinary tract infection in the prior month.
- Have douched or used any vaginal products**,** including lubricants, feminine hygiene products, vaginal drying agents and sex toys during the 48 hours prior to enrollment.
- Have had sexual intercourse during the 48 hours prior to enrollment.
- Have evidence of acute or chronic hepatitis B infection (defined as + HBV core IgM, + HBV core IgG or + HBsAg).
- Have evidence of liver or kidney abnormalities (defined as ALT or AST >2x normal, Total bilirubin >1.2 mg/dl, and creatinine >1.2 mg/dl).
- Oral antibiotics in the past 7 days.

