**9.3 Pregnancy**

If a participant is found to be pregnant at the screening or enrollment visits, she will discuss the results with the clinician and will not continue in the study. She will be referred for care by the study clinicians. If she becomes pregnant during the course of the study, she will discontinue study product and be referred for care. The study team will attempt to obtain pregnancy outcome data on any women who become pregnant while on study drug.

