**Appendix I. Schedule of assessments**

|  | **Screening** | **Enrollment**  **(Day 0)** | **Day 3** | **Day 7** | **Day 14** | **Final Visit (Day 21)** |
| --- | --- | --- | --- | --- | --- | --- |
| Informed Consent | X |  |  |  |  |  |
| Sexual History | X | X*b* | X*b* | X*b* | X*b* | X*b* |
| Medical History/Concomitant Meds | X | X*b* | X*b* | X*b* | X*b* | X*b* |
| HIV EIA | X |  |  |  |  |  |
| Provide HIV/STI pre-test counseling | X |  |  |  |  |  |
| Provide HIV/STI test results and post-test counseling |  | X |  |  |  |  |
| Urine Microscopy/Culture | X |  |  |  |  |  |
| Urine pregnancy test | X | X |  |  |  |  |
| Serum pregnancy test | X |  |  |  |  |  |
| Pelvic Exam | X | X | X | X | X | X |
| Bimanual examination | X |  |  |  |  |  |
| Pap smear*c* | X |  |  |  |  |  |
| Vaginal pH | X | X | X | X | X | X |
| Wet Mount (*Trichomonas*, *Candida*, BV) | X | X | X | X | X | X |
| Inspection for sperm on wet mount and PSA | X | X | X | X | X | X |
| Herpes simplex virus culture | X*a* | X*a* | X*a* | X*a* | X*a* | X*a* |
| *N. gonorrhoeae/C. trachomatis* | X | X*a* | X*a* | X*a* | X*a* | X*a* |
| Progesterone and Estradiol | X | X |  | X | X |  |
| Serum tenofovir level |  | X | X | X | X | X |
| Liver function tests (ALT, AST, total bilirubin, hep B surface ant, hep B core IgM, hep B core IgG ) | X |  |  |  |  |  |
| Kidney function tests | X |  |  |  |  |  |
| *T. pallidum* (RPR) | X |  |  |  |  |  |
| Herpes simplex virus serology | X |  |  |  |  |  |
| CVL collection | X | X | X | X | X | X |
| Record Adverse Events |  | X | X | X | X | X |
| Distribute study supplies |  | X |  |  |  |  |
| Distribute Participant Diary |  | X |  |  |  |  |
| Review Participant Diary |  |  | X | X | X | X |
| Count used & unused supplies |  |  | X | X | X |  |

*a*If clinically indicated

*b*Interim history collected

*c*A Pap smear will be obtained if documentation of a negative result within the last year is not available

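### The pregnancy rules in 5.2, 9.3, 9.6 and 9.7 rest on a finding that no scheduled procedure after Day 0 produces, and the 48-hour pre-enrolment abstinence rule leaves a small conception window open

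*Protocol*

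**What the plan says.** **Who may enrol.** Section 5.1 counts as low risk a woman "Being either sexually abstinent or being in a stable, mutually monogamous relationship with a partner who is not known to be HIV positive". Section 5.2 excludes women who "Are currently using hormonal contraception or have used hormonal contraception in the previous 2 months". Neither section requires a non-hormonal method.

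**Abstinence.** Section 5.1 requires that participants "Agree to abstain from sexual intercourse and to not use vaginal products for 48 hours prior to enrollment", and sets the whole period as "for 48 hours prior to enrollment and for the duration of the study (through the Final Visit"). Section 4.0 gives the same start and end: "from 48 hours prior to the enrollment visit until completion of the study".

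**Timing.** Sections 4.0 and 7.1 place Day 0 two to six days after menses end. Section 4.0 targets the Final Visit at Day 21 (range 16 to 21), "prior to the anticipated onset of menstruation".

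**Pregnancy testing.** In Appendix I the row reads "Urine pregnancy test | X | X", for Screening and Day 0, and its remaining cells are empty. The serum test is at Screening only. The Day 3, 7, 14 and 21 procedure lists in 7.1 contain no pregnancy test.

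**Pregnancy rules.** Section 5.2 lists pregnancy, determined by urine test, among exclusions that apply at screening, at enrolment and at any time during participation. Section 9.3 states: "If she becomes pregnant during the course of the study, she will discontinue study product and be referred for care". It adds that outcome data will be sought for women who become pregnant on study drug. Pregnancy is also a criterion for stopping treatment in 9.6 and for leaving the study in 9.7.

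**The concern.** Four sections act on a pregnancy during the study, but the schedule stops looking for one at the moment dosing starts. The protocol does allow for abstinence failing. It repeats the sperm and PSA checks at every visit, has the diary record vaginal penetration (4.0), and records breaches on case report forms (6.4). Even so, no pregnancy test follows.

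The eligibility window adds to this. A woman in a relationship, not using hormonal contraception, may have intercourse after menses and until 48 hours before Day 0. A urine test on Day 0 would be expected to be negative for a conception only days old (an assumption; the documents do not address it). Because the Final Visit precedes expected menses and ends participation, a missed period would normally appear only after the last visit. At stake is exposure of an early pregnancy to up to 14 doses in a Phase I study that treats pregnancy as disqualifying throughout.

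**Working it through.** **Step 1. Rule against schedule (no assumption needed).** Pregnancy tests scheduled after Day 0: Day 3 none, Day 7 none, Day 14 none, Day 21 none, so 0 of 4 visits. The rule in 5.2 is framed as a urine-test finding at any time during participation. The schedule can produce that finding only at Screening and Day 0.

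**Step 2. Can permitted intercourse before Day 0 lead to conception?**

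From the protocol:
- Day 0 is 2 to 6 days after menses end.
- The last permitted intercourse is 2 days before Day 0.
- The Final Visit is on study Day f, with f between 16 and 21, and precedes menses.

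Assumed, not in the documents:
- Ovulation is a = 14 days before the next menses.
- The fertile window opens w = 5 days before ovulation.

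Let Day 0 be cycle day d and let the cycle last L days.

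- The fertile window opens on cycle day L − a − w = L − 19.
- Permitted intercourse reaches it if d − 2 ≥ L − 19, that is **L ≤ d + 17**.
- A Final Visit on Day f precedes menses if **d + f ≤ L**.
- Both hold only if d + f ≤ d + 17, that is **f ≤ 17**. Menses length drops out.

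With f at least 16, the compatible cycles are L = d + 16 to d + 17. For menses of 5 days (assumed):

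| Enrolment | d | Last permitted intercourse | Compatible L |
|---|---|---|---|
| Earliest (2 days after menses) | 7 | cycle day 5 | 23–24 |
| Latest (6 days after menses) | 11 | cycle day 9 | 27–28 |

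At the target f = 21, L must be at least d + 21. The window then opens no earlier than d + 21 − 19 = d + 2, which is four days after the last permitted intercourse at d − 2. There is no overlap.

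**Step 3. Sensitivity.** In general the condition is f ≤ a + w − 2.

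| a | w | Latest compatible Final Visit | Within Days 16–21? |
|---|---|---|---|
| 14 | 3 | Day 15 | No |
| 14 | 5 | Day 17 | Day 16–17 only |
| 16 | 5 | Day 19 | Day 16–19 only |

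None of these reaches Day 21.

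**Step 4. Grid check.** Six cycle lengths (21, 24, 26, 28, 32, 35), three menses lengths (3, 5, 7) and earliest or latest enrolment give 6 × 3 × 2 = 36 scenarios. These are counts, not probabilities.

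- With the 5-day window, permitted intercourse reaches the fertile window in 17 of 36.
- Of those 17, 12 leave no room for even a Day 16 Final Visit before menses. Five remain, as (cycle, menses, days from menses end to Day 0): (21, 3, 2), (24, 5, 2), (26, 3, 6), (26, 7, 2) and (28, 5, 6).
- The first of the five allows a Final Visit no later than Day 16 and the others no later than Day 17. None allows Day 21.
- With the 3-day window, 12 of 36 overlap and none fits, because f would have to be at most 15.

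**Step 5. Is Day 16 or 17 reachable?** Yes. Section 4.0 allows the Final Visit from Day 16. Section 7.1 schedules it 3 to 8 days after the Day 14 visit, so an on-target Day 14 visit permits Day 14 + 3 = Day 17.

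**The case against.** The strongest reply is that the visit schedule already screens out most of the risk. Dosing is meant to fall between menses, and 7.1 times Day 0 so as to secure 21 days without bleeding. A woman who truly completes Day 21 before menses cannot, under the stated assumptions, have conceived from permitted pre-enrolment intercourse. That stands, and it governs the size of the point. A reader might infer from the 48-hour rule alone that every cycle of up to 28 days is exposed. The documents do not support this, because most such cycles leave no room for the Final Visit before menses.

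There are also other safeguards: abstinence through the Final Visit, exclusion at Day 0 on sperm or PSA findings, serum as well as urine testing at Screening, enrolment soon after an observed menses, and refusal of women unsure they can decline intercourse (8.3). These reduce the risk. They do not close it, and a semen check is not a pregnancy test.

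Finally, 9.3 is a contingency rule and does not by its terms need a scheduled test. A reader might infer that a pregnancy could never trigger it. That goes too far: medical history is updated at each visit, and 7.2 allows interim visits at any time. The objection is weaker against 5.2, which ties the exclusion to a urine test.

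**Conclusion.** The point holds in a limited form. As a matter of text, no scheduled procedure after Day 0 would detect a pregnancy, although 5.2, 9.3, 9.6 and 9.7 act on one. This rests on no assumption.

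As a matter of risk, the pre-enrolment window is narrow. With ovulation 14 days before menses and a 5-day fertile window, it opens only when the Final Visit falls on Day 16 or 17, and it is closed at the target Day 21. A 3-day window closes it altogether, and a 16-day interval from ovulation to menses extends it to Day 19. Ovulation earlier or later than assumed, or a breach of abstinence during the study, lies outside this arithmetic. The documents give no basis for a probability.

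This is a matter of participant safety and consistent eligibility rules. A reader might infer that early pregnancies would also distort the mediator results, but the documents give no figure for such an effect. The point does not bear on the sample size or the analysis.

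**What to change.** 1. Reconcile the pregnancy provisions in 5.2, 9.3, 9.6 and 9.7 with Appendix I and the visit lists in 7.1, so that the rule rests on something the schedule can produce. Which way to reconcile them is a clinical decision for the sponsor and the investigator.
2. Reconcile the start of pre-enrolment abstinence in 4.0, 5.1 and 7.1 with the timing of Day 0, so that the interval after the preceding menses is covered. Compliance can be checked in the interim sexual history already taken at Day 0.

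The second change needs no new procedure. Its cost is a few extra days of abstinence per participant and possibly a few lost volunteers. The cost of the first depends on how the sponsor resolves it.
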